**Fig. 2 Fig2:**
[figure not shown]
The schedule of enrolment, interventions and assessments. *-t*_*0*_ during the process of enrolment, *t*_*0*_ baseline, *t*_*1*_ after completion of exercise intervention (equivalent to the end of the patients’ first-line chemotherapy), *t*_*2*_ 6 months after completion of exercise intervention, *HIIT* high-intensity interval endurance training; *Placebo* control group training (supervised myofascial release training), *HVLT-R* Hopkins Verbal Learning Test - Revised, *COWAT* Controlled Oral Word Association Test, *TMT* Trail Making Test part A/part B, *INHIB* Response Inhibition Test, *FACT-COG* Functional Assessment of Cancer Therapy – Cognitive function, *TNF-α* tumor necrosis factor alpha, *IL-6* Interleukin-6, *IL-1α* Interleukin-1 Alpha, *IL-1β* Interleukin-1 Beta, *CRP* C-reactive protein*, IL-1RA* Interleukin-1 receptor antagonist, *IL-10* Interleukin-10, *BDNF* brain-derived neurotrophic factor, *VEGF* vascular endothelial growth factor, *IGF-1* insulin-like growth factor 1, *IXT* incremental exercise test, *MFI-20* The multidimensional Fatigue Inventory, *EORTC-QLQ-C30* core questionnaire 30 items of the European Organization for Research and Treatment of Cancer, *HADS-D* German version of the Hospital Anxiety and Depression Scale *PSQI* Pittsburgh Sleeping Quality Index. * As demographic data: age, sex, education, socioeconomic status will be captured. ** As anthropometric data height, weight and BMI will be captured

### Primary endpoint

The primary endpoint of the present study will be the change of test-scores from baseline (t_0_) to after completion of the exercise intervention (t_1_), in the test battery recommended by the International Cancer and Cognition Task Force (ICCTF) to capture CRCI [59]. The ICCTF test battery comprises of the Hopkins Verbal Learning Test – Revised (HVLT-R), Trail-Making-Test A/B (TMT-A/TMT-B) and the Controlled Oral Word Association Test (COWAT).The HVLT-RThe HVLT-R was developed to measure forgetfulness in the domain of verbal memory in individuals at the age of 16 and older [67]. The test includes a list of 12 nouns, which will be read to the participants. Then, the participants will be instructed to repeat as many words from that list as they can remember in any order. This process will be repeated three times. The sum of correct recalled words at all 3 learning trials (“Total-Recall”) has been described as measure of learning efficiency and short-term verbal memory [68] and will be used for analyses. The HVLT-R offers six parallel forms. As recommended for repeated testing, the parallel forms 1, 2 and 4 will be used at t_0_, t_1_ and t_2_ [68]. The order of test forms at the 3 measurement time points will be random but counterbalanced across participants. The HVLT-R shows adequate psychometric properties [69, 70].TMT-A/BThe TMT-A will instruct participants to connect randomly distributed numbers from 1 to 25 as quickly and as correctly as possible, in ascending order. The time participants require for completing TMT part A has been described as a valid measure of selective attention [71] and will be used for analyses in the planned study. TMT-B will instruct participants to connect randomly distributed numbers (1 to 13) and letters (A to L) in ascending order, alternating between numbers and letters as quickly and as correctly as possible. The time participants require for completing TMT part B has been reported as valid measure of executive functioning subdomain set-shifting [71] and will be used for analyses. In the present study, the Langensteinbacher version of the TMT (TMT-L) [72] will be applied. It will be operated via the Wiener Test-System (WTS) (Schuhfried, Vienna, Austria) and adequate psychometric properties have been reported for it [72]. TMT-L parallel versions S1, S2 and S3 will be used in a random order at the 3 measurement time-points, but counterbalanced across participants.COWATThe German version of the COWAT will be used in the present study [73]. Participants will be instructed to name as many words as possible in one min, beginning with a given letter. As recommended in the German test-manual [73], the letters S, P and M will be used at the 3 measurement time points. The order of the letters will be random, but counterbalanced across participants. The number of words participants will produce will be used for analyzation. Adequate psychometric properties for the German version of the COWAT have been reported [73].

### Secondary endpoints

The following secondary endpoints will be assessed in the present study:Go-/No-Go-test performanceThe Response Inhibition Test (INHIB) [74] will be applied as additional cognitive test in the planned study. It will also be operated via the WTS. The INHIB is a classical Go-/No-go test paradigm. Participants will be presented with Go- and No-Go-stimuli. They will be instructed to push a button, as quickly as possible, as a response to a Go-stimulus. The vast majority of stimuli will be Go-stimuli, forming a response tendency of pushing the button. The number of erroneous reactions to No-go-stimuli has been reported as valid measure of executive functioning subdomain response inhibition [71] and will be used for analyses. Adequate psychometric properties have been reported for the INIHIB [75].Self-perceived cognitive performanceSelf-perceived cognitive performance will be assessed using the FACT-COG questionnaire (German Version 3) [76], which was developed as part of the Functional Assessment of Cancer Therapy-Measurement System [77]. The FACT-Cog version 3 is comprised of 37 items, with 4 subscales: patients’ perceived cognitive impairments, deficits observed or commented by others, perceived cognitive abilities, impact of cognitive changes on quality of life. Respondents will indicate the frequency of each occurrence over the 7 days preceding the test, using a 5-point Likert-type scale ranging from 0 (never) to 4 (several times). For the FACT-Cog adequate psychometric properties have been reported [78].Inflammatory marker, neurotrophin and growth factor expressionSerum levels of TNF-α, IL-6, IL-1α, IL-1β, CRP, IL-1RA and IL-10 as well as of BDNF, IGF-1 and VEGF will be quantified by using enzyme-linked immunosorbent assay (ELISA). Drawing of 8.5 ml venous blood at resting state will be performed at t_0_, t_1_ and t_2_. Samples will be taken from a peripheral vein of the arm and collected in serum gel tubes (S-Monovette® Serum, Sarstedt, Nümbrecht, Germany). After complete coagulation at 4 °C, samples will be centrifuged for 10 min at 1000 g and 4 °C. The serum will be prepared and aliquoted within 24 h after blood drawing and duplicate samples will be stored at − 80 °C until analyzed when samples of all included participants will be collected.Patients’ physical fitnessPatients’ physical fitness will be assessed using an incremental exercise test (IXT) on a bicycle ergometer (Ergoselect 100 Typ K, Ergoline, Bitz, Germany). According to recommended guideline [79], a quasi-ramp protocol will be used, starting at 20 W (W) and increasing intensity for 10 W every minute until pulmonic or muscular exhaustion. Patients will be advised to pedal at 60 to 70 rpm. During IXT, blood pressure will be monitored using the ergometer module for automatic blood pressure management. Heart rate and cardiac rhythm will also be monitored during IXT using a 12-lead ECG (Amedtec CardioPart Blue, Amedtec, Aue, Germany). Oxygen uptake and carbon emission during IXT will be recorded using spirometry (Amedtec Ergostik, Amedtec, Aue, Germany). When patients will reach voluntary exhaustion, 20 μl of capillary blood will be withdrawn from patient’s earlobe to determine whole blood lactate concentration. Patients’ maximal performance will be defined reaching one of the following criteria: (1) capillary lactate levels of ≥8 mmol/L; (2) respiratory exchange ratio of ≥1.1; (3) maximum heart rate of 220 minus age ± 10 min^− 1^; (4) rate of perceived exertion on Borg scale ≥18 [80–82]. Incremental exercise test will be conducted under the supervision of a physician. As measures of physical fitness, patients’ maximal performance in watts per kilogram bodyweight (W/kg), as well as their peak of oxygen uptake (VO_2peak_) in milliliter oxygen uptake per kilogram bodyweight per minute, will be calculated for each participant.Other common cancer related side effectsAssessment of patients’ anxiety and depression will be done according to the German version of the Hospital Anxiety and Depression Scale (HADS-D, “D” is indicating the German version of the HADS) [83]. Patients’ fatigue will be assessed using the German 20 item version of the Multidimensional Fatigue Inventory (MFI-20) [84]. Patients’ quality of sleep will be assessed using the German version of the Pittsburgh Sleep Quality Index [85]. Patients’ quality of life will be assessed by using the EORTC QLQ-C30 questionnaire and the updated breast cancer module QOL-BR23 [86]. In addition, assessment of the chemotherapy completion rates and adverse effects will be done via medical records.Sustainability of effects of HIIT on CRCISix months after completion of the HIIT/placebo intervention (equivalent to the end of the patients’ first-line chemotherapy), the ICCTF test-battery will be additionally applied to assess the sustainability of potential positive effects of the HIIT on CRCI compared to placebo.

### Testing procedure

All assessments will take place at the Clinic Northwest in Frankfurt (Germany). In order to control for potential diurnal rhythms of biomarkers, the testing appointments will always be scheduled at 8.00 o’clock in the morning. Patients will be instructed to fast for at least 12 h before the testing appointment and to bring breakfast food along. First, an 8.5 ml fasting venous blood sample will be taken. Subsequently, patients will be given time to have breakfast. Then, patients will fill in the questionnaires (FACT-COG, EORTC QLQ-C30, QOL-BR23, PSQI, HADS-D, MFI-20). After a 15-min break, the first neuropsychological testing block comprising of the HVLT-R and the TMT will take place. It will last approximately 20 min. After another 15-min break, the second neuropsychological testing block will be conducted, applying the COWAT and the INHIB. It will take approximately 15 min. After completion of the neuropsychological testing, the IXT will be conducted lasting approximately 30 min.

### Adverse events and compliance assessment

Adverse events (AE), as well as serious adverse events (SAE), related to the exercise intervention will be assessed by the attending physicians at the Clinic Northwest in Frankfurt (Germany). Compliance to HIIT and control group intervention will be protocolled by scientific staff. It is pre-defined that patients need to participate on average in 2 exercise sessions per week following the above described treatment protocol for complete compliance. It has been shown feasible in previously published studies [51]. However, in case of emerging limitations to follow the protocol, these limitations will be addressed. The exercise regimen will be (temporarily) adapted and the patients will continue the program to the maximum extent possible.

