### Study population and recruitment

Participants will be recruited at the Department for Oncology and Hematology of the Clinic Northwest and at the Department for Gynecology at the University Clinic in Frankfurt (Germany). Patients with initial diagnosis of mammary carcinoma stage I-IIIA and scheduled chemotherapy, not fulfilling any of the listed exclusion criteria in Table 2, will be recommended for study participation by the attending physician to the principal investigator. Patients will receive detailed descriptions of the study and will be given sufficient time to ask any questions. Patients will be included in the planned study only after they will give written informed consent. The participants will be included chronologically.

**Table 2 Tab2:** Objectives and hypotheses of the study

Objectives	Hypotheses
Main objective • To evaluate the effects of a HIIT versus placebo, conducted simultaneously with first-line chemotherapy regimen on CRCI, in women with breast cancer	Main hypothesis • In women with breast cancer, the decline in HVLT-R-, TMT-A/B- and COWAT test performance from baseline to completion of the exercise-intervention, is significantly smaller in the HIIT group compared to the control group (hypothesis A)
Secondary objective • To evaluate the effects of a HIIT versus placebo, conducted simultaneously with first-line chemotherapy regimen on self-perceived cognitive performance, in women with breast cancer	Secondary hypotheses • In women with breast cancer, the decline of FACT-COG scores from baseline to completion of the exercise-intervention/to 6-months follow-up^a^_,_ is significantly smaller in the HIIT group compared to the control group (hypothesis B)
• To evaluate the effects of a HIIT versus placebo, conducted simultaneously with first-line chemotherapy regimen on executive functioning subdomain response inhibition, in women with breast cancer	• In women with breast cancer, the decline of INHIB performance from baseline to completion of the exercise-intervention/to 6-months follow up, is significantly smaller in the HIIT group compared to the control group (hypothesis C)

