### Groups and interventions

Patients will be allocated either into a HIIT or a placebo control group. High-intensity interval endurance training and placebo control group will be conducted at the Clinic Northwest in Frankfurt (Germany), simultaneously with the patients’ first-line chemotherapy regimen, typically lasting 12 to 18 weeks.HIIT GroupPatients will receive a supervised HIIT on a stationary bicycle ergometer (Ergoselect 100 Typ K, Ergoline, Bitz, Germany). Sessions will be carried out 3 times per week with at least 24 h rest between sessions. The first 5 min (min) of each training session will be warm-up at low-intensity (cadence at 60–70 rpm (rpm) and wattage according to 57–63% of patient’s maximum heart rate (HR_max_)). During the first 8 weeks of patients’ chemotherapy, HIIT will consist of 3 × 3 min high-intensive intervals (cadence at 80–100 rpm and wattage according to 85–90% of HR_max_) interspersed by 90 s active rest-intervals (cadence at 60–70 rpm and wattage according to 57–63% of HR_max_). During the second half of patients’ chemotherapy, the number of intervals will be increased to 5 [49]. The last 5 min of each training session will be cool-down at low-intensity (cadence at 60–70 rpm and wattage according to 57–63% of HR_max_). Accordingly, duration of each HIIT session will be approximately 20–25 min during the first 8 weeks of patients’ chemotherapy and 30–35 min during the second half of patients’ chemotherapy. In cases of participants showing blunted heart rate response to exercise, (i.e. resulting from medications like beta-blocker medication) ratings of perceived exertion on the Borg scale [60] will be used to control exercise intensity rather than heart rate [61]. In such cases, warm up, cool down and active rest intervals, interspersed between high-intensive intervals, will be conducted at wattage in accordance with a rating of perceived exertion of 10–12 on the Borg scale. High-intensive intervals, in such cases, will be conducted at wattage in accordance with a rating of perceived exertion of 16–18 on the Borg scale. Any deviations from the protocol will be recorded. High-intensity interval endurance training will be conducted in addition to the standard medical treatment and physiotherapy.Placebo Control Group (PCG)Patients allocated to the PCG will receive a supervised myofascial release training 3 times per week with at least 24 h rest between sessions. The training sessions consist of seven standardized exercises using a foam roll (Blackroll, Bottighofen, Swiss): self-massage of the soles of the feet (standing on one leg), of the calves (lying in dorsal position), of the hamstrings (lying in dorsal position), of the thighs (manually while lying in dorsal position), of the neck (lying in dorsal position), of the lower and upper back (leaning backwards against a wall in standing position), as well as self-massage of the upper arm and shoulder (leaning sideways against a wall in standing position). During the first 8 weeks of patients’ chemotherapy, each exercise will be repeated 6 times on each side of the body. During the second half of patients’ chemotherapy, each exercise will be repeated 10 times on each side of the body. Between each exercise, participants will do low-intense shoulder and hip mobilization exercises for 2 min. Accordingly, duration of each PCG session will be approximately 20–25 min during the first 8 weeks of patients’ chemotherapy and 30–35 min during the second half of patients’ chemotherapy. Any deviations to this protocol will be recorded. Myofascial release training will also be conducted in addition to the standard medical treatment and physiotherapy.

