
PCG-training was designed as attention control condition. Both treatments, HIIT and PCG-training, will be carried out individually and will be supervised by independent sport-therapists. Training frequency and duration of HIIT and PCG training sessions will be equal, to ensure that the attention, the treatment contact and the nonspecific therapist effects are balanced between HIIT group and PCG. However, PCG-training (myofascial release training), unlike the HIIT, will induce hardly any muscular effort and cardiovascular stimulation [62].

Exercise-treatments will be carried out neither on chemotherapy days, nor 24 h after a chemotherapy application [63]. Other contraindications that prohibit participation in a training session of HIIT or PCG are described below:InfectionsHemoglobin < 8 g per deciliterPlatelet counts < 10,000/μlFeverNauseaDizziness

Patients’ compliance to the exercise program will be strengthened by the individual supervision patients receive. Each patient will have one sport-therapist that will run all the training sessions. The sport-therapist will monitor the patient’s exercise sessions closely and will motivate the patient to apply the protocol. The sport-therapist will provide feedback on patients’ progress and will discuss benefits and barriers of the exercise with the patient. Feedback and support from sport-therapists have been reported to promote adherence to exercise programs in breast cancer patients [64, 65]. To further increase adherence to the training, participants will receive an E-mail every Friday afternoon by their sport-therapist summarizing their previous workout and reinforcing patients’ adherence by praising their attendance and discipline in the program. The E-mail will also contain the training schedule for the following week with the days and times of the planned training sessions.

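### The adverse event section limits AE and SAE assessment to events judged exercise-related, and the record-based adverse effects item does not clearly fill the gap, so the harms comparison between arms is open to attribution bias

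*Protocol article*

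**What the plan says.** Two places in the protocol article deal with harms.

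- **Adverse events and compliance assessment** states: "Adverse events (AE), as well as serious adverse events (SAE), related to the exercise intervention will be assessed by the attending physicians". The physicians are those at the Clinic Northwest. The relatedness condition covers serious events as well as non-serious ones.
- **Secondary endpoints**, in the item on other common cancer-related side effects, states: "In addition, assessment of the chemotherapy completion rates and adverse effects will be done via medical records". No relatedness condition, arm or clinic is attached.

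The arms differ sharply in exertion. Groups and interventions sets the HIIT intervals at 85–90% of maximum heart rate and says that the control training "will induce hardly any muscular effort and cardiovascular stimulation". The opening of Methods calls both arms forms of supervised exercise, so the AE/SAE rule formally applies to each.

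On blinding, Randomization and blinding keeps participants unaware of the hypotheses as far as possible, and Statistical analysis describes a blinded statistician. Nothing is said about the physicians who assess adverse events.

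**The concern.** Relatedness is normally judged after an event has been recorded. Here it is part of the definition of what is assessed, so the content of the AE/SAE assessment depends on a causal opinion, and that opinion can depend on the arm.

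The bias can run in either direction:

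- A collapse or palpitation is more readily blamed on near-maximal cycling than on foam rolling. That would inflate the recorded events under HIIT.
- All patients are on chemotherapy. A genuine HIIT harm that looks like chemotherapy toxicity, such as an infection or a cardiac symptom, may be judged unrelated and left out. That would hide an excess.

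The trial evaluates HIIT as a supportive therapy during chemotherapy. Any benefit on cognition will be weighed against harms, and a harms comparison that mixes true risk with arm-dependent attribution is a poor basis for that. It cannot be repaired at analysis if events judged unrelated were never assessed.

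**Working it through.** **The two places side by side**

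| | Adverse events and compliance assessment | Secondary endpoints |
|---|---|---|
| Term used | AE and SAE | adverse effects |
| Relatedness condition | exercise-related | none stated |
| Source | attending physicians, Clinic Northwest | medical records, clinic not stated |
| Context | the section devoted to adverse events | cancer side effects, paired with chemotherapy completion |

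Neither place refers to the other. The matching secondary measure in the Abstract, the Background and the objectives table is chemotherapy compliance; none of the three lists adverse events as an outcome. The record-based item therefore reads most naturally as chemotherapy tolerability. A wider reading is possible, but the text does not settle it.

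**Illustration of the mechanism**

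The plan gives no event or attribution rate, so those below are assumptions. The arm size comes from the plan: 118 × 1.15 = 135.7, rounded to the stated 136; equal allocation gives 136 / 2 = 68 per arm.

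*Equal true risk.* Assume that 20% of patients in each arm have an event: 68 × 0.20 = 13.6 per arm. Recorded events = 13.6 × the share attributed to exercise.

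| Attributed, HIIT / control | Recorded, HIIT | Recorded, control | Ratio |
|---|---|---|---|
| 10% / 10% | 1.36 | 1.36 | 1 |
| 10% / 5% | 1.36 | 0.68 | 2 |
| 30% / 10% | 4.08 | 1.36 | 3 |
| 30% / 5% | 4.08 | 0.68 | 6 |

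The true ratio is 1 in every row. The recorded ratio is simply the ratio of the two assumed attribution shares.

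*True excess under HIIT.* Assume true rates of 30% and 20%, with the same attribution share *a* in both arms. Recorded excess = *a* × (30 − 20) percentage points.

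- *a* = 5%: 0.5 points, so 95% of the excess is lost.
- *a* = 10%: 1 point (3% against 2%), so 90% is lost. In patients, 68 × 0.30 × 0.10 = 2.04 against 68 × 0.20 × 0.10 = 1.36.
- *a* = 30%: 3 points, so 70% is lost.

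With equal attribution the ratio of 1.5 survives, but at 10% attribution it rests on about two events against one. Both illustrations describe the exercise-related assessment alone and give no credit to the medical-record item.

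**The case against.** A reader might infer that only exercise-related events are collected anywhere, so that harms cannot be compared at all and an unexpected harm of HIIT would go uncounted. The documents do not support that. The record-based item has no relatedness filter, and Data collection and timeline has all secondary measures re-assessed after the intervention and at six months. A harm entered in the records could therefore be collected and compared by arm. Coverage is unclear, not excluded. Nor does the adverse event section say outright that other events go unrecorded; it says which ones the physicians assess.

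A reader might also infer that events in patients from the second recruiting clinic are lost, because the assessing physicians are at one clinic only. That is weak. Both arms train at the Clinic Northwest (Groups and interventions), and all assessments take place there (Testing procedure). The point matters only for events seen solely at the University Clinic.

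Three further objections deserve an answer:

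- *The rule is the same in both arms.* True, and injuries during foam rolling could be attributed to it. But an identical rule does not make the judgement identical when the exertion differs so much and blinding of the assessors is not described.
- *No listed hypothesis compares adverse events.* True; hypotheses A to N are unaffected. What suffers is the harms evidence against which a benefit will be weighed.
- *A journal article condenses the full protocol.* This rightly excuses missing detail on grading scales, reporting windows or forms. It does not excuse a scope that the article states and that is itself the difficulty.

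**Conclusion.** The concern holds in limited form. The AE/SAE assessment, as worded, is conditional on judged relatedness, by physicians whose blinding is not described, in arms that differ greatly in exertion. It cannot support an unbiased comparison of harms. The medical-record item may soften this but does not clearly cover all AEs and SAEs, and the article does not say how the two sources fit together.

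The size is unknown. The recorded ratios of 1 to 6, and the loss of 70–95% of a true excess, follow entirely from assumed event and attribution rates and should not be read as estimates for this trial. The conclusion itself rests on two judgements: that attribution is likely to differ between HIIT and foam rolling, and that the record-based item is chiefly about chemotherapy tolerability. The first is plausible but not demonstrated in the documents; the second is the more natural reading but not the only one. The primary cognitive analysis is not affected.

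**What to change.** Reconcile the adverse event section with the record-based item in Secondary endpoints. State that:

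1. all AEs and SAEs are recorded in both arms, regardless of relatedness;
2. the sources are the supervised training contacts and the medical records, including those of the University Clinic for patients treated there;
3. relatedness is graded afterwards, as an attribute of each recorded event;
4. the arms are compared on all events, with exercise-related events shown as a subset.

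Grading scales and reporting windows can stay in the full protocol.

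The cost is a change of wording and a longer event form. Therapists are already scheduled to see each patient three times a week, and medical records are already a data source. The downside is more events to enter, most of them chemotherapy-related. The change concerns data collection only and leaves the interventions as they are.
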